**Study Design**

We are conducting an observational “natural experiment” study and developing a policy impact model. The key intervention – Opiate Substitution Treatment (OST) can no longer be randomised with a placebo control, and no earlier trials of OST were large enough to assess mortality as the outcome(3). Therefore, we are exploiting information (that was not collected specifically for research) on variation in exposure and outcome derived from administrative databases. We will extract and analyse an open observational cohort based on Clinical Practice Research Datalink (CPRD) primary care database.

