**Study population**

The study population comprise all patients aged 16-64 who have been prescribed methadone or buprenorphine as opiate substitution treatment (OST) in CPRD practices from 1997 to 2014, including a sub-set of patients eligible for ONS linkage. opiate dependent people treated with opiate substitution drugs on CPRD. The table shows the initial set of criteria. Prescription dose and diagnoses will be checked to confirm that prescription for OST and to exclude any patients prescribed for pain/analgesia.

| **prodcode** | **Productname** |
| --- | --- |
| 3064 | Buprenorphine 400microgram sublingual tablets sugar free |
| 3522 | Temgesic 200microgram sublingual tablets (RB Pharmaceuticals Ltd) |
| 6056 | Buprenorphine 8mg sublingual tablets sugar free |
| 6210 | Subutex 8mg sublingual tablets (RB Pharmaceuticals Ltd) |
| 6547 | Buprenorphine 2mg sublingual tablets sugar free |
| 7457 | Temgesic 0.3mg/ml Injection (Reckitt Benckiser Healthcare (UK) Ltd) |
| 8017 | Temgesic 400microgram sublingual tablets (RB Pharmaceuticals Ltd) |
| 10077 | Subutex 2mg sublingual tablets (RB Pharmaceuticals Ltd) |
| 13031 | Subutex 0.4mg sublingual tablets (RB Pharmaceuticals Ltd) |
| 35269 | Temgesic 300micrograms/1ml solution for injection ampoules (RB Pharmaceuticals Ltd) |
| 40211 | Buprenorphine 2mg sublingual tablets sugar free (Teva UK Ltd) |
| 40212 | Buprenorphine 8mg sublingual tablets sugar free (Teva UK Ltd) |
| 40473 | Buprenorphine 300micrograms/1ml solution for injection ampoules |
| 35169 | Suboxone 8mg/2mg sublingual tablets (RB Pharmaceuticals Ltd) |
| 35170 | Suboxone 2mg/500microgram sublingual tablets (RB Pharmaceuticals Ltd) |
| 35681 | Buprenorphine 2mg / Naloxone 500microgram sublingual tablets sugar free |
| 35682 | Buprenorphine 8mg / Naloxone 2mg sublingual tablets sugar free |
| 38311 | Naloxone hc 2mg + 8mg Tablet |
| 42074 | Naloxone hc 500micrograms + 2mg Tablet |
| 2952 | Methadone 1mg/ml oral solution |
| 5211 | Methadone 2mg/5ml linctus |
| 5322 | Physeptone 5mg tablets (Martindale Pharmaceuticals Ltd) |
| 6441 | Methadone 5mg tablets |
| 9728 | Methadone 1mg/ml oral solution sugar free |
| 11722 | Methadone 10mg/ml oral solution sugar free |
| 14086 | Methadone 10mg/ml Injection |
| 17671 | Methadone 50mg/1ml solution for injection ampoules |
| 17896 | Physeptone 10mg/ml Injection (Martindale Pharmaceuticals Ltd) |
| 21562 | Physeptone 1mg/ml mixture sugar free (Martindale Pharmaceuticals Ltd) |

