**Exposures, outcomes and covariates**

*Exposure:-* OST includes methadone and buprenorphine and occasionally dihydrocodeine(6, 11). Intervention exposure is defined by prescribing data collected by primary care practices contributing information through their electronic health record systems to the Clinical Practice Research Datalink (CPRD). This will include information on all prescriptions in primary care plus other information on diagnoses and attendances at primary care and hospital. We will extract information on patients on the basis that they have a drug misuse diagnosis and have been prescribed methadone or buprenorphine. Some patients also may have been prescribed dihydrocodeine as OST – and so we will include these treatment episodes as well. The information provided by CPRD will allow us to establish when OST started, changes in dose or type of OST, and when OST ceased. For each treatment period we will classify different periods “on”/during or “off”/after OST or other drug treatment e.g. 1st 2 weeks of treatment, rest of time on treatment (baseline treatment period), 1st 4 weeks after treatment, and rest of time out of treatment (censored at 12 months after last prescription); as well as measure average OST duration and classify treatment duration (≤ 1 month, 2-6 months, 7-12 months, 12+months).

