*Main outcome:* All and cause specific death (in particular drug poisoning/overdose) during drug treatment or follow-up period up to one year after date of last opiate substitution treatment (OST) prescription/treatment admission. Standard codes for drug related poisonings deaths will be used to define overdose deaths (23): ICD-10 codes: F11-16; F18-19; X40-44; X60-64; X85; Y10-14; as well as in terms of general and specific drugs mentioned on the death certificate (any opiate, heroin and Morphine, Methadone, buprenorphine, dihydrocodeine, other opiods, cocaine, all amphetamines and MDMA, GHB, GBL, all benzodiazepines, barbiturates, all antidepressants, paracetamol and other over the counter medicines). We will categorise deaths as “avoidable” and “preventable” based on ONS definitions (<http://www.ons.gov.uk/ons/publications/re-reference-tables.html?edition=tcm%3A77-262418>). Other specific causes that will be investigated include suicide and other injury (non drug related poisoning), infectious diseases, cirrhosis and liver disease. All cause mortality will be expressed as a rate and as a Standardised Mortality Ratio (SMR) compared to standard age and sex death rates for England and Wales. Cause specific mortality will be expressed as rates – and SMRs also will be calculated for non-drug related poisonings. Follow-up of patients extracted from primary care database (Clinical Practice Research Datalink, CRPD) will be from date of first OST prescription within risk period beginning 1990 to end 2011. A patient’s follow up will cease either one year after the expiry of their last prescription for OST or the date of death or on the date of transfer out from the general practice or risk study period end (which ever date occurs first). [Follow-up of patients extracted from Drug Data Warehouse (DDW) will be from 2005 to 2009 the period for which National Drug Treatment records are linked to the mortality register.] We are censoring follow-up twelve months after last prescription or specialist drug treatment date in order to reduce potential bias.

Secondary outcomes concern the practice and delivery of OST including:- annual number of people in OST; modality/specific OST drug; duration of OST; dose; evidence of reaching optimal dosage, tapering OST dose towards planned discharge, and supervised consumption; and co-prescription of benzodiazepines.

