**Use of linked data**

We will use the ONS mortality file to define overdose and drug related mortality. Previously supplied data in 2014 provided fewer deaths than expected with only 30% of deaths in the OST sample being identified as overdose or drug related. This left analyses underpowered to detect expected effect sizes. The new linkage data, set 11 covering a greater number of practices and a longer time span, offers the potential to overcome the limitations of our current data set.

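### The follow-up rule has no end date for the practice's prescribing data, so a patient still on OST when those data end is counted as having stopped

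*Protocol*

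**What the plan says.** In the Protocol, the main-outcome paragraph of Exposures, outcomes and covariates fixes when follow-up ends. For each person, "follow up will cease either one year after the expiry of their last prescription for OST or the date of death". Two administrative dates complete the list: the rule adds that follow-up can also stop "on the date of transfer out from the general practice or risk study period end (which ever date occurs first". That is a complete list of four dates with an earliest-date rule. Patients enter at their first OST prescription "within risk period beginning 1990 to end 2011".

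The exposure paragraph of the same section says that exposure is "defined by prescribing data collected by primary care practices contributing information through their electronic health record systems". After the last prescription, a patient's time is divided into the first 4 weeks after treatment and the remaining time out of treatment, up to 12 months.

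Other sections give a different calendar window. Study population describes patients prescribed OST "in CPRD practices from 1997 to 2014, including a sub-set of patients eligible for ONS linkage". The sample-size section runs from 1998 to 2014, and the amendment of 3 November 2014 from 1997 to 2014.

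For the parallel Drug Data Warehouse (DDW) cohort, the main-outcome paragraph limits follow-up to 2005-2009 and gives the reason: those are the years in which treatment records are linked to the mortality register. It makes no such statement for the CPRD cohort.

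**The concern.** Stopping OST is inferred from the absence of a further recorded prescription. That inference is sound only while the practice is still supplying prescribing data. The rule protects a patient who is on OST at study end, because follow-up is cut there and no stop is inferred. It gives no such protection when the practice's data end earlier. Transfer out is an event in the patient's registration and does not clearly cover a practice that ceases to contribute.

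The first weeks after cessation are a period whose raised risk the study sets out to corroborate (Limitations). False stops add time there from people who may still be in treatment. They also shorten recorded treatment duration, and the resulting estimates feed the population model. The Poisson, self-controlled case-series and marginal structural analyses all take treatment history from the same records, so agreement between them would not reveal the error.

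A second and distinct gap concerns outcomes. If CPRD follow-up runs past ONS coverage, person-time accrues, on or off treatment, in which cause-specific deaths cannot be seen.

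**Working it through.** **Inputs from the Protocol.** Sample size: 20,000 patients; about 32,000 person-years on treatment and 35,000 off; fatal overdose 0.8% out of treatment, stated to be twice the risk in treatment, hence 0.4% in treatment. Background: mortality soon after cessation more than 8 times that during treatment, taken here as 8.

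**The Protocol's own figure.** 32,000 + 35,000 = 67,000 person-years, as stated. The on/off split cannot be derived from the document.

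**Assumptions.** The share *f* of patients still on OST when their practice's data end before study end is not given, so a range is shown. Each such patient is taken to contribute one full false off-treatment year (4 + 48 weeks), to remain in fact on treatment, and to have the on-treatment risk. The 0.8% and 0.4% are read as rates per person-year.

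**Formulas.**
- False off-treatment time: m = f × 20,000 × 1 year.
- Apparent off/on ratio, deaths still captured: [(35,000 − m) × 0.8% + m × 0.4%] / 35,000 / 0.4%.
- Apparent ratio, deaths in the false time not captured: (35,000 − m) × 0.8% / 35,000 / 0.4%.

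For f = 5%: m = 1,000, or 1,000/35,000 = 2.9% of off-treatment time. The numerator with deaths captured is 34,000 × 0.008 + 1,000 × 0.004 = 276 deaths; 276/35,000 = 0.789%, and 0.789/0.4 = 1.97.

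For f = 10%: m = 2,000 (5.7%). The numerator is 264 + 8 = 272; 272/35,000 = 0.777%, and the ratio is 1.94.

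| f (assumed) | False person-years | Share of 35,000 | Ratio, deaths captured | Ratio, deaths not captured |
|---|---|---|---|---|
| 2% | 400 | 1.1% | 1.99 | 1.98 |
| 5% | 1,000 | 2.9% | 1.97 | 1.94 |
| 10% | 2,000 | 5.7% | 1.94 | 1.89 |
| 20% | 4,000 | 11.4% | 1.89 | 1.77 |
| 30% | 6,000 | 17.1% | 1.83 | 1.66 |

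**First 4 weeks after treatment.** If a share *s* of that window is false and deaths are captured, a true ratio of 8 appears as 8(1 − s) + s: 7.65 at s = 5% and 7.30 at s = 10%. Here *s* is a share of stops, not of patients. A practice's data can end only once for a patient, so repeated treatment episodes make *s* smaller than *f*.

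**Linkage, by comparison of the text.** The DDW cohort is explicitly bounded by its mortality linkage. The CPRD cohort is bounded by a study end that is end 2011 in one place and 2014 in three others. The document does not say whether either date is the end of ONS coverage.

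**The case against.** The strongest reply is that the problem rests on an assumption. Nothing in the Protocol shows that any practice's data stop before study end. An open cohort does not establish it. The December 2015 amendment describes a newer linkage set "covering a greater number of practices and a longer time span", but that compares two supplies of linked data and is silent on prescribing data. If no practice leaves early, no false stop arises by this route. This stands, and the frequency must be read as unknown.

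It can also be said that Limitations already plans sensitivity analyses on the definition of on and off treatment, with missing quantity or dose given only as an example. That is fair, but changing the definition does not clearly help when the last recorded prescription is itself produced by the data ending.

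A third reply is that a last-data date is an operational field for a statistical analysis plan. That would hold if the Protocol were silent. Here it states a complete rule, and applied as written the rule misclassifies these patients.

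On linkage, the study end may be meant as the limit of ONS coverage. That is possible, but the conflicting dates leave it open. ONS data are also clearly needed only for cause of death, so the claim that deaths go unseen is firm only for cause-specific mortality.

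Three stronger readings are tempting and are not supported:
- A reader might infer that loss of ONS linkage is also analysed as stopping OST. It is not: exposure comes from prescribing data alone.
- A reader might infer a bias between methadone and buprenorphine. The documents give no basis for its existence or direction, and calendar year is a planned adjustment.
- A reader might gauge the dilution by setting the 4.6% post-treatment risk against 0.69%. The former belongs to a comparison by treatment duration and the latter is the risk on methadone, so their ratio is not a post-cessation effect.

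**Conclusion.** The point holds in a limited form and should be corrected. The written rule turns the end of a practice's data into an apparent end of OST, and no other section puts this right. The resulting bias is towards the null and modest. With 5-10% of patients affected, at most 3-6% of off-treatment time is false, and an off/on ratio of 2.0 is seen as about 1.97-1.94 if deaths are still captured (1.94-1.89 if they are not). It becomes material only if many more patients are affected.

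These figures rest on an assumed share and on affected patients remaining in treatment. The person-years are upper bounds, because study end will cut some of the false years short.

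The linkage gap is a separate and less certain matter: the end of CPRD follow-up in relation to ONS coverage is unresolved, not shown to be wrong.

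**What to change.** In the main-outcome paragraph of Exposures, outcomes and covariates:

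1. Add the last date on which the practice supplied prescribing data to the list of follow-up end dates.
2. State that no off-treatment window is opened when the last prescription's expiry, plus the gap used to define stopping, falls after that date.
3. State that follow-up for linked outcomes ends when ONS coverage ends, as is already done for the DDW cohort.
4. Reconcile the study period there (1990 to end 2011) with the sample-size section, Study population and the November 2014 amendment (all to 2014).

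It would also help to report how many patients were on OST at their practice's last data date, since that replaces the assumed share above with a fact.

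The cost is a sentence or two and two date fields. The downside is slightly fewer off-treatment person-years, including those of some patients who really did stop shortly before their practice's data ended.

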In the UK OST has expanded 5-fold in the last 10 years to over 1800kg per year (roughly equivalent to 33.3 million doses per year)(19). The rate of methadone deaths per gram of methadone prescribed has fallen, coinciding and attributed to the issuing and implementation of clinical guidelines recommending greater supervised consumption(20), but trends in the overall number of opiate related deaths have not declined (21) (22). Therefore, we aim to examine in more detail the risk of death during and after OST and other drug treatment in order to assess how changing the delivery of drug treatment could reduce the number of drug related deaths in the population.

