- Is there evidence that delivery of OST in primary care has changed over time – specifically in terms of changes in:- average dose and % of patients receiving optimal OST dose; OST modality; number and % of patients undergoing a planned discharged over time; number and % receiving co-prescription of benzodiazepines; number and % with evidence of supervised consumption.

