*Covariates/confounders:-* Additional exposures (benzodiazepines, treatment performance/quality) and confounders (age, gender, co-morbidity as defined by Charlson Index(24), alcohol and mental health problems, treatment episode number, calendar year, other prescription drugs) all of which have been shown to influence mortality risk(11) (9). Supervised prescription will need to be coded through analysis of free-text – which will be piloted and developed with CPRD. A sample of records with full free text will be used to identify key words and search terms that can define the variable “evidence of supervised consumption”. The key words and search terms can then be used across the whole database to record the covariate.

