Fourth, even in the absence of unmeasured confounding, conventional methods (eg regression models that control for baseline or time-dependent confounders) will provide estimates that may fail to have a causal interpretation when (i) there is a measured time-dependent risk factor for survival that also predicts subsequent treatment, and (ii) past treatment history predicts the subsequent level of this risk factor. We will use inverse probability (IP) weighted estimation of marginal structural models, which avoids conditioning on time-dependent confounders(33, 34). Instead, we estimate the inverse of each patient’s probability of their observed treatment history at each time. By weighting a marginal model according to the reciprocal of these probabilities, we mimic a situation in which the assignment to treatment is at random (or unrelated to the time-varying covariates).

By examining the intervention effects between exposure and outcome and how they vary across multiple methods which adjust for confounding in different ways we will be able to assess the likelihood that residual/time-varying confounding remains a significant problem, and to contribute stronger evidence on the impact of treatment on drug related mortality(35, 36). Similar analyses will be conducted on the risk of mortality during and after exposure to non-pharmacological treatments(18).

2) The secondary analysis of clinical databases will test whether there have been changes over time in the number of patients treated over time and specifically in the delivery of OST in primary care (e.g. the mean dose, treatment duration, modality and evidence of supervised consumption). Segmented regression techniques will be used for time trend analyses of these treatment indicators in order to test whether there have been changes over time, and whether the timing of the change is consistent with issuing of new treatment guidelines(20, 37).

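### A change in how often supervised consumption is written down at a guideline date can look like a change in delivery, and the planned trend test cannot separate the two

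*Protocol*

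**What the plan says.** Four parts of the protocol bear on this.

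- **Measurement (Exposures, outcomes and covariates, paragraph on covariates).** "Supervised prescription will need to be coded through analysis of free-text – which will be piloted and developed with CPRD". The terms come from a subset of records whose free text is available in full, and "The key words and search terms can then be used across the whole database to record the covariate". No structured field for supervision is named.
- **Use as an outcome (Objective, specific aims and rationale; Main outcome).** One question asks how the "number and % with evidence of supervised consumption" changed over time. Supervised consumption is listed among the secondary outcomes on how OST is practised and delivered.
- **Trend test (Data/ Statistical Analysis Plan, item 2).** The delivery indicators are "e.g. the mean dose, treatment duration, modality and evidence of supervised consumption". Their trends are to be analysed by segmented regression, and the analysis asks "whether the timing of the change is consistent with issuing of new treatment guidelines". References 20 and 37 are cited here.
- **Content of the guidelines (Background).** Citing the same reference 20, the protocol attributes a fall in methadone deaths per gram prescribed to the "issuing and implementation of clinical guidelines recommending greater supervised consumption".

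The variable has a second use. A question under Objective, specific aims and rationale asks whether overdose and drug-related death at the start and end of treatment are lower in patients with evidence of supervision.

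**The concern.** An indicator built from free text responds to two things: what patients received, and what was written about it. A guideline that recommends supervision may change both, and possibly at the same date. If only the writing changes, the indicator still moves at the date the plan examines, and the result would be read as delivery having responded to guidance.

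The described pilot finds search terms. It is not said to measure how completely supervision is recorded, or whether that differs by calendar period. The Limitations section plans sensitivity analyses for a similar problem, missing prescription data that blur on and off treatment, but does not mention completeness of free text.

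For the mortality question, supervised patients with no matching text may fall into the comparison group and dilute any effect of supervision.

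**Working it through.** The protocol states no figure on this point, so there is none to reproduce. The check asks what the planned indicator does when only recording changes.

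**Inputs.** From the protocol: about 32,000 on-treatment person-years, 1998 to 2014 (Sample size/power calculation), which is 17 calendar years, so 32,000 / 17 ≈ 1,882 per year. Reference 37 is the 2007 UK clinical guidelines. Everything else is assumed: true supervised share 20%, 40% or 60%; recording probability 30% to 60%; no false positives; a break after 2007; each person-year counted as one patient.

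**Step 1, the identity.** Recorded share = true share × recording probability. Two different histories give the same series:
- Delivery constant, recording doubles: 0.40 × 0.30 = 12%, then 0.40 × 0.60 = 24%.
- Recording constant, delivery doubles: 0.40 × 0.30 = 12%, then 0.80 × 0.30 = 24%.

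No regression on the recorded share alone can distinguish them, and a larger sample does not help.

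**Step 2, what segmented regression would report.** A logistic model with trend, step and slope change was fitted to 17 simulated yearly counts of about 1,882. True supervision was constant and recording changed only at the break (1,000 simulations per setting, two-sided 5% test of the step).

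| Recording | True share | Recorded share | Apparent odds ratio for the step | Step significant |
|---|---|---|---|---|
| 30% throughout | 20 / 40 / 60% | 6 / 12 / 18%, unchanged | 1.00 | 4.3 / 5.3 / 5.4% |
| 30% to 40% | 20% | 6% to 8% | 1.36 | 93.0% |
| 30% to 40% | 40% | 12% to 16% | 1.40 | 99.9% |
| 30% to 40% | 60% | 18% to 24% | 1.44 | 100% |
| 50% to 60% | 20% | 10% to 12% | 1.23 | 80.2% |
| 50% to 60% | 40% | 20% to 24% | 1.26 | 98.8% |
| 50% to 60% | 60% | 30% to 36% | 1.31 | 100% |
| 30% to 60% | 20 / 40 / 60% | doubles | 2.15 / 2.32 / 2.56 | 100% |

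**Step 3, the mortality question.** Suppose the true rate ratio for supervision is 0.50, recording is 30%, recording is unrelated to risk, and unrecorded supervised patients sit in the comparison group. With true share p, the comparison group's rate relative to unsupervised patients is [0.7p × 0.5 + (1 − p)] / [0.7p + (1 − p)].
- p = 20%: 0.87 / 0.94 = 0.926; observed ratio 0.50 / 0.926 = 0.54
- p = 40%: 0.74 / 0.88 = 0.841; observed ratio 0.50 / 0.841 = 0.59
- p = 60%: 0.61 / 0.82 = 0.744; observed ratio 0.50 / 0.744 = 0.67

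**Step 4, does restricting to recorded arrangements repair the trend?** Keep a true share of 40% and recording of supervision rising from 30% to 60%. Assume unsupervised arrangements are written down 10% of the time throughout, which gives 0.60 × 0.10 = 6%. The restricted share moves from 0.12 / 0.18 = 67% to 0.24 / 0.30 = 80%. That is a 13-point artefact, against 12 points in the whole-cohort share. The restriction works only if both kinds of recording change in the same ratio. The not-recorded share moves from 100 − 12 − 6 = 82% to 100 − 24 − 6 = 70%, so the shift becomes visible.

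**The case against.** The strongest defence is that the protocol is modest on this point. It speaks of evidence of supervision throughout, asks only whether timing is consistent with guidelines, and leaves the coding to a pilot with CPRD. Sampling frame, coding levels and validation are details that a pilot or an SAP usually settles. Much of this stands. A reader might infer that the sample is unstratified, that the variable is yes/no, or that a record without a match counts as unsupervised. The protocol says none of these things; they are readings of its silence.

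A reader might also infer that recording did change and that any observed step will be an artefact. Nothing in the documents shows this, and every prevalence and recording probability above is assumed. A gradual drift in recording would go largely into the slope; a false step needs a fairly abrupt change near the tested date.

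On mortality, calendar year is among the planned adjustments, which partly deals with years of poorer recording. It does not correct misclassification within a year, but under the assumptions above that error pulls the estimate towards no effect and does not create one.

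What survives is that the protocol itself fixes one set of terms for the whole database, treats the result as an indicator of delivery, and tests it against guideline timing, with no stated check on recording.

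**Conclusion.** The point holds as a conditional risk of bias. The recorded share confounds delivery with documentation, and segmented regression cannot separate them at a guideline date. If recording did step up there, even a rise of 10 percentage points would usually give a significant step (80% to 100% of simulations), and a doubling of recording would double the indicator. The true size is unknown.

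The reach is limited to one secondary outcome and one additional exposure. The Limitations section names buprenorphine versus methadone mortality as the key hypothesis, and the documents give no reason to extend this concern to that comparison. For the supervision question, the expected consequence is an understated effect: 0.54 to 0.67 in place of an assumed 0.50 at 30% recording.

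**What to change.** - Draw the planned free-text pilot sample by calendar period, before and after each guideline date, and by drug. Build the term list from all strata and report how well it matches hand-read records in each period.
- Code three levels: supervised, explicitly not supervised, and not recorded. Keep not recorded as its own category in the mortality models.
- Keep the whole-cohort share as the trend series and report the not-recorded share by year beside it. Show the share among recorded arrangements only as a sensitivity analysis, because it is biased when the two kinds of recording change unequally.
- Describe the result as a trend in recorded evidence. Do not attribute a step to changed delivery if the not-recorded share shifts at the same date.

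The cost is some extra coding in a pilot that is already planned, and a weaker conclusion about delivery. Two limits remain. Hand-reading checks the terms against what was written and cannot recover supervision that nobody wrote down. The not-recorded share can also shift when delivery truly changes: in the 40% to 80% example at 30% recording, with 10% recording of unsupervised arrangements, it moves from 82% to 100 − 24 − 2 = 74%. It therefore limits what may be claimed and does not identify the cause.
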